### Data collection

Data on recruitment, including number of eligible and consenting patients and reasons for non-consent, will be collected. Patient demographic data including age, gender, ICU admission diagnosis, co-morbid diseases, date of admission to ICU, ICU length of stay, hospital length of stay, hospital discharge destination and support level required on discharge from hospital will be collected from the medical records. Severity of illness will be measured using the Acute Physiology and Chronic Health Evaluation II (APACHE II) scoring system [59].

Duration of mechanical ventilation will be extracted from the Australia New Zealand Intensive Care Society ANZICS Adult Patient Database (APD). The time schedule for enrollments and administration of assessments and outcome measures is illustrated in Table 4. Retention data including number of withdrawals and reason for withdrawal will be collected. Data will be collected using multiple formal case report forms (CRFs) including pre-screening measures (inclusion/exclusion criteria on all screened patient admissions), admission demographics, pre-intervention checklist for decision making regarding therapy implementation, daily intervention pre- and post-measures, daily control group measures and collation of outcome measures at the three time points. The formal CRFs will be transcribed to an excel spreadsheet for analysis post trial completion. Data forms will be reviewed weekly by the primary investigator to ensure missing data occasions are minimised. Clinical case notes will be audited using a data collection audit checklist.

**Table 4 Tab4:** Time schedule of enrolment and assessments for participants

Measure	Enrolment	Allocation to intervention	ICU Stay	ICU discharge	Hospital discharge	Follow up 90 days
Eligibility screen	x					
Informed consent	x					
Informant Questionnaire on Cognitive Decline in the Elderly (IQCODE)	x					
Demographic		x				
APACHE II		x				
Modified Barthel Index (MBI)	x (Reported)			x	x	x
Grip Strength (Dynamometer)				x	x	x
Functional Independence Measure (FIM)				x	x	x
Short Form (SF-36v2)				x		x
Hospital Anxiety and Depression Scale (HADS)				x	x	x
Confusion Assessment Measure (CAM-ICU)			Daily			
Glasgow Coma Scale (GCS)			Daily			
Short Portable Mental Status Questionnaire (MSQ)			Daily			
Richmond Agitation and Sedation Scale (RASS)			Daily			
Montreal Cognitive Assessment (MoCA)				x	x	x
Dose of Occupational Therapy			Daily			
Intervention fidelity checking through notes audit			Daily			

### Outcome measures

#### Primary outcome measure

Independence within activities of daily living will be measured using the Functional Independence Measure (FIM™). The FIM will quantify the participant’s functional and cognitive status at intensive care unit and hospital discharge, as well as at 90 days post-randomisation. This tool is validated for use in the critically ill population [60, 61] and provides reliable information regarding patient functional change during rehabilitation across various hospital and community settings [62]. The FIM will be conducted within 24 h of the expected discharge from the intensive care unit and hospital or on the Friday before the expected discharge, if likely to occur over the weekend. It will also be administered during the 90-day follow-up session. The FIM will be performed by an occupational therapist blinded to participant assignment groups and who does not actively work on the intensive care unit.

#### Secondary outcome measures

The Modified Barthel Index (MBI) [63] is used to measure functional ability and serves as a secondary measure included for its ability to detect change within self-care and functional tasks. The MBI is commonly used in hospital settings, although recent research has highlighted ceiling effects and lack of reliability [64]. The MBI also provides an additional source of comparison across multiple earlier critical care rehabilitation studies. The MBI will be used at multiple time points including allocation to intervention, intensive care unit discharge, hospital discharge and 90-day post-randomisation follow-up.The Montreal Cognitive Assessment (MoCA) [65] is a screening measure of cognition and assesses multiple domains of cognition including attention, memory and visuospatial relations. It is commonly used within the acute and community setting and demonstrates high criterion and convergent validity within the acute care setting [66]. The MoCA will be administered at discharge from intensive care unit, hospital and 90-day post-randomisation follow-up using alternate versions at each time point [67].Grip strength will be measured using a dynamometer (Jamar) [68] at discharge from intensive care unit and hospital and 90-day post-randomisation follow-up. Grip strength is used as a measure of intensive care unit-acquired weakness (ICUAW) and infers a relation between weakness and inability to complete functional activities independently [69].The Short-Form (36) Health Survey (SF-36v2™) will provide a baseline and post discharge measure of participants’ health-related quality of life (HRQOL). The SF-36v2™ is a validated and reliable tool [70] and has been further validated within the critical care setting [71]. This will be completed at intensive care unit discharge and 90-day post-randomisation follow-up.Sedation and delirium status will be measured using the validated Richmond Agitation Sedation Scale (RASS) [46] and the reliable and validated Confusion Assessment Method for ICU (CAM-ICU) [50]. These scores are regularly administered by nursing staff throughout a 24-h period. RASS and CAM-ICU scores immediately prior to and following early occupation-based interventions will be collected for additional analysis. RASS and CAM-ICU scores for the control group participants will be collected daily at 9am.The Glasgow Coma Scale (GCS) [72] is used to evaluate the level of consciousness in patients with neurological conditions or severe injury [73] and will be collected daily at 9 am in the control group, and pre-treatment in the intervention group.Hospital Anxiety and Depression Scale (HADS) [74] is a measure of emotional distress regarding anxiety and depression. It has been validated with the use of critical care survivors [75]. It will be administered at discharge from intensive care unit, hospital and 90-day post-randomisation follow-up.The Informant Questionnaire on Cognitive Decline in the Elderly (IQCODE) (short form) [76] is a reliable and validated measure used to screen for cognitive dysfunction. It will be used as a screening tool for eligibility to the trial and will be completed by the participant’s person responsible.The Short Portable Mental Status Questionnaire (MSQ) [51] is a brief orientation checklist used to demonstrate current and previous memory linked to orientation. It is a 10-statement questionnaire that is easily administered at the bedside. It will be completed pre-and post-treatment in the intervention group, and at 9 am in the control group.

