### Participants

The study will be conducted in a Queensland level two adult eight-bed intensive care unit at Logan Hospital, Brisbane, Australia. All patients admitted to the intensive care unit will be included if they are aged over 18 years and are expected to require invasive mechanical ventilation for greater than 48 h.

Patients will be excluded from the trial if:
They are admitted to the intensive care unit but do not require mechanical ventilation.They have been readmitted to the intensive care unit from the current hospitalisation.A withdrawal of treatment is expected to occur within the next 24 h or they are not expected to survive the current intensive care unit admission.They have a poor level of functional ability prior to admission (requiring carer assistance/high dependency level in activities of daily living as measured by a Modified Barthel Index score < 40).They have a pre-existing severe cognitive deficit (as identified by completion of the short form IQCODE with an average score above 3.31–3.38).They have a pre-existing significant mental health disorder impacting on participation.They live interstate and would be unable to attend the 90 days post-randomisation follow-up in person.They are unable to communicate in English.

Patients admitted over the weekend where occupational therapy intervention cannot be immediately initiated will be eligible to participate in the trial, and therapy will begin on the first working day.

The 90-day post-randomisation evaluations’ timepoint for the follow-up review date has been chosen based on the funding cycle. As this is a pilot feasibility study and the study is limited in duration, this time point was chosen to be sufficiently representative to identify if patients had ongoing concerns, and to ensure their memory of the therapy provision was current for the semi-structured interviews.

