### Randomisation and blinding

Following consent, participants will be randomly allocated to either the intervention group who will receive early occupation-based activity or the control group who will receive standard occupational therapy, medical, nursing and physiotherapy care. Patients will be randomised into the intervention and control groups via computer-generated numbers (http://www.randomization.com/) which will be sealed in consecutively numbered opaque envelopes. The production of the envelopes will be performed by research support staff who will not be involved in the interventions.

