### Data analysis

All data from the case report forms (CRF) will be entered into a purposefully designed Excel database and exported into SPSS version 22.0 for analyses. Descriptive statistics will be used to determine the distributions of the data for the intervention and control groups and to test whether statistical assumptions for parametric tests are achieved. Imputation will be used to correct for missing data. Continuous variables that are normally distributed will be compared between the groups at each follow-up using an independent groups *t* test. Effect sizes will be calculated using Cohen’s *d*. Non-parametric analysis will be conducted for continuous variables that are not normally distributed. Categorical variables will be compared with the chi-square statistic. A *p* value of 0.05 will be considered statistically significant. Where appropriate, analyses will be reported with mean differences and 95% CI. Previous values from the same patient will be used for missing data.

In particular, objectives will be analysed as follows:
The utility of the selection of outcome measures will undergo sensitivity analyses in relation to the ease with which they can be administered and will relate to missing data and the identification of both univariate and multivariate outliers. The effect size for the primary outcome variable will be used to determine the required sample size for a fully powered trial.Recruitment and consent rates will be collected and analysed to determine the feasibility of recruiting form the chosen population. The inclusion and exclusion data (screening log) will be summarised and will influence further protocol changes when considering progression to a full scale randomised controlled trial.Retention rates in response to follow-up procedures (attendance at interviews) will be analysed to identify any trends that may influence further trial progression.The intervention data will undergo sensitivity analyses in relation to non-compliance, the intention to treat per protocol in addition to as treated. Protocol violations regarding the intervention manual strategies will be noted.The intervention effect will be analysed through the use of the above outcome measures, and further analysis of case notes will reveal common trends in treatment adaptation or selection, based on the structure of the intervention manual.

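### The outcome text and Table 4 place the first Modified Barthel Index (MBI) differently, and the missing-data rule could enter that first score as an ICU-discharge outcome

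*Protocol article*

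**What the plan says.** All references are to the protocol article.

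- **Secondary outcome measures:** "The MBI will be used at multiple time points including allocation to intervention, intensive care unit discharge, hospital discharge and 90-day post-randomisation follow-up". Allocation stands in one series with the three outcome assessments, and nothing says whether that score is reported or observed. The section says that the MBI "serves as a secondary measure included for its ability to detect change within self-care and functional tasks".
- **Data collection, Table 4:** enrolment and allocation have separate columns. Demographics and APACHE II are ticked at allocation. The MBI is not; its first entry is under enrolment, marked as reported. The later entries are at ICU discharge, hospital discharge and 90 days.
- **Participants:** patients with poor function before admission are excluded: "requiring carer assistance/high dependency level in activities of daily living as measured by a Modified Barthel Index score < 40". Those included are "expected to require invasive mechanical ventilation for greater than 48 h".
- **Randomisation and blinding:** "Following consent, participants will be randomly allocated". No interval between consent and allocation is given.
- **Data analysis:** "Continuous variables that are normally distributed will be compared between the groups at each follow-up using an independent groups" *t* test. The same section says that missing data will be filled with the patient's own earlier values and sets no limit on which earlier value qualifies.

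**The concern.** The text and the schedule give different time points for the first MBI, and only the schedule says what kind of score it is. A reported score describes function before the illness. A score observed at allocation would describe a patient in intensive care who is expected to need ventilation for more than 48 h. Staff working from the two places could record different quantities in the same field.

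This reaches the written analysis through the missing-data rule. In Table 4 the FIM, MoCA, grip strength, HADS and SF-36 all start at ICU discharge, so none of them has an earlier value to carry into that time point. The MBI has one. If the ICU-discharge MBI is missing, the rule as written would enter the first MBI, whichever quantity that is. If hospital discharge is missing as well, the same value passes on to that time point.

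**Working it through.** The plan states no MBI mean, standard deviation or change, so there is no figure to reproduce. The check compares the two places and then sizes the effect of carrying the first score forward.

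**1. Schedule**

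| Time point | Outcome text | Table 4 |
|---|---|---|
| Enrolment | not listed | yes, reported |
| Allocation | yes, type not stated | blank |
| ICU discharge | yes | yes |
| Hospital discharge | yes | yes |
| 90 days | yes | yes |

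The two agree on the three outcome assessments and disagree only on the first score.

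**2. Candidate values for the first score**

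- Reported pre-admission score: at least 40, because lower scores are excluded (Participants).
- Score observed at allocation: probably near the bottom of the scale. This is an assumption; the document gives no such value.
- Gap between the two: about 40 points if the observed score is 0 and the pre-admission score is 40. An observed score of 10 would reduce this to 40 − 10 = 30. A higher pre-admission score would widen it.

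**3. Effect on an arm mean at ICU discharge**

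Inputs: 30 patients allocated 1:1, so 15 per arm (Design; Sample size). The number missing, k, is assumed to be 1 to 3, because the plan gives no rate for ICU discharge.

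Difference in arm mean between the two readings = (k / 15) × gap.

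| k | gap 30 | gap 40 |
|---|---|---|
| 1 | 1/15 × 30 = 2.0 | 1/15 × 40 = 2.7 |
| 3 | 3/15 × 30 = 6.0 | 3/15 × 40 = 8.0 |

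Equal numbers missing in both arms would largely cancel in the between-arm difference. Unequal numbers would not: with 3 missing in one arm and 1 in the other, a 40-point gap moves the difference by (3 − 1)/15 × 40 = 5.3 points.

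**4. Aligning the schedule is not enough**

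Assume an observed ICU-discharge mean of 50 and 25% missing, the loss that the 75% retention target in Table 1 would allow, borrowed here for illustration.

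- Filled with 0: 0.75 × 50 + 0.25 × 0 = 37.5.
- Filled with 40: 0.75 × 50 + 0.25 × 40 = 47.5.
- Filled with 100: 0.75 × 50 + 0.25 × 100 = 62.5.

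Even when the first score is settled as the pre-admission one, the filled mean depends on function before the illness and not on function at ICU discharge.

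**The case against.** The strongest reply is that the document gives two labels for one score. Allocation follows consent, a pre-admission MBI is needed before anyone can enter, and the table that serves as the time schedule marks the only pre-treatment MBI as reported. On that reading the outcome text is merely loose. This may well be right, and the fix adopts it. The text still needs to say so, because it names a column that the table leaves empty.

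A reader might go further and infer that the trial has two opposed baselines, so that MBI change reverses sign according to the passage followed. The document does not support that. It never says that the allocation score is observed at the bedside. It names no analysis of MBI change: groups are compared on scores at each follow-up, and that test does not reverse. Describing the MBI as able to detect change explains the choice of instrument and does not specify a change analysis. If change were analysed, randomisation would leave the expected between-arm difference the same under either baseline.

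It is also fair to say that the main fault lies in the carry-forward rule. That part stands: the fix must reach the Data analysis section as well as the outcome text. Finally, this is a secondary outcome in a 30-patient feasibility trial. The primary outcome, the progression criteria and the sample size are untouched.

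**Conclusion.** The inconsistency is confirmed: the outcome text puts the first MBI at allocation, and Table 4 puts it at enrolment as a reported score. The planned comparisons of observed follow-up scores are unaffected. The consequence is confined to missing ICU-discharge MBIs (and later ones with no intervening score), which the Data analysis rule would fill with a value that is not a valid post-ICU outcome under either reading.

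The illustrative size is about 2.7 to 8 points on an arm mean. It rests on three assumptions: 1 to 3 of 15 values missing, an observed allocation score near zero, and a pre-admission score of about 40. It is not a lower bound, since a higher allocation score shrinks it. The point is modest, but it is cheap to correct and removes a biased imputation.

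**What to change.** 1. In Secondary outcome measures, state that the pre-treatment MBI is the reported pre-admission score taken at enrolment, as in Table 4. List ICU discharge, hospital discharge and 90 days as the outcome time points. Say that the pre-admission score serves eligibility and baseline description or covariate adjustment.
2. In Data analysis, state that this score is not carried forward to fill a missing post-ICU MBI.
3. Keep the between-group comparison of MBI scores at the three follow-ups. Do not use ICU discharge as the baseline for a change score: the intervention is delivered in the ICU, so any effect already present at discharge would be subtracted out.

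The cost is a revised sentence in one section and an added one in another, with whatever ethics and registry notification the Ethics/governance section requires. No new data are needed, because eligibility screening already uses the score.

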Patients will undergo sedation breaks during which targeted early enhanced occupation-based therapy will be delivered. The therapist will carry out the intervention to a maximum of 60 min per day, based on graded performance and localised adaptation from response level, such that sessions may be carried out twice a day (30 min each) to 3 times a day (20 min each) or a single session with a higher level patient (60 min). The measure of 60 min has been chosen to comply with perceived expectations of rehabilitation unit therapy intensity and duration per profession [45]. Where the full quota of therapy is unable to be provided, clear reasons for therapy termination will be gathered on the data form and analysed.

Prior to engaging the patient in early enhanced occupation-based therapy, participants will undergo simple cognitive and physical assessments to enable the therapist to adapt the chosen task to optimise performance and ensure that cognitive stimulation is appropriate. Pre-intervention measures include the following:

Richmond Agitation and Sedation Scale (RASS) [46] measures level of sedation and agitation. Patients will receive treatment if they fall within − 2 to + 2 scales. Patients falling on either extremes are deemed unsuitable for engagement at the current time point, although will be assessed regularly throughout the day prior to therapy, to ensure all opportunities for engagement are taken.

Glasgow Coma Scale (GCS) [47] measures arousal and response level in patients with severe injuries and is used to identify initial emergence of recovery post-sedation withdrawal. The highest score is 15 (fully oriented and alert) and the lowest score is 3 whereby a patient is considered unresponsive. The GCS will be completed prior to the treatment intervention as this will guide the therapist in providing either sensory stimulation [48, 49] or early enhanced occupation-based therapy.

The Confusion Assessment Measure ICU (CAM-ICU) [50] is an assessment of confusion in the early identification of delirium of patients within the intensive care unit. The presence of delirium will not limit participation within an early enhanced occupation-based therapy session. Strategies will be used to increase attention and encourage sequencing of short subtasks in order to complete a full grooming or self-care task.

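### Daily RASS, CAM-ICU, GCS and MSQ are read at 9 am in controls but around therapy sessions in the intervention arm, so a between-arm comparison of them can be expected to be biased

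*Protocol article*

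**What the plan says.** All in the Protocol article.

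- **RASS and CAM-ICU** (Secondary outcome measures). Controls: "RASS and CAM-ICU scores for the control group participants will be collected daily at 9am". Intervention arm: "RASS and CAM-ICU scores immediately prior to and following early occupation-based interventions will be collected for additional analysis". The same paragraph says of routine charting: "These scores are regularly administered by nursing staff throughout a 24-h period".
- **GCS** (same section): "will be collected daily at 9 am in the control group, and pre-treatment in the intervention group".
- **MSQ** (same section): "It will be completed pre-and post-treatment in the intervention group, and at 9 am in the control group".
- **When sessions happen** (Intervention group): "Patients will undergo sedation breaks during which targeted early enhanced occupation-based therapy will be delivered". A session needs a RASS from −2 to +2. Otherwise: "Patients falling on either extremes are deemed unsuitable for engagement at the current time point, although will be assessed regularly throughout the day". There may be one to three sessions a day.
- **Days covered** (Recruitment): occupational therapy cover is Monday to Friday.
- **Use of the scores** (Data analysis): the intervention effect is to be examined with the outcome measures listed earlier in the article, by group comparisons at a p value of 0.05.
- **Table 4** schedules all four scores daily during the ICU stay and does not separate the arms.

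**The concern.** Randomisation makes the patients comparable. It does not make the readings comparable when the rule for taking them depends on the arm. Here four things differ by allocation: clock time, sedation state at the reading, the days that yield a reading, and the number of readings per day. A control is scored at 9 am in whatever state he or she is in. An intervention patient's session scores exist only once a treatable state has been found, possibly after several looks that day.

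The first Part 1 objective is to judge how well the chosen measures capture the effect of the intervention. A score that separates the arms because of when it was read could look responsive and be carried into the phase III design on that basis. The reverse error is also possible, because more readings give more chances to detect delirium.

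**Working it through.** **Step 1. Reading rules side by side.**

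| | Control | Intervention |
|---|---|---|
| RASS, CAM-ICU | 9 am, daily | before and after each session |
| MSQ | 9 am, daily | before and after treatment |
| GCS | 9 am, daily | before treatment only |
| State at reading | not restricted | sedation break; RASS −2 to +2 at session start |
| Days | daily | session days, with cover Monday to Friday |
| RASS/CAM-ICU readings per day | 1 | up to 3 sessions × 2 = 6 |

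The article names no common time or window for any of the four scores. The routine nursing scores could supply one for RASS and CAM-ICU, but they are not named as the source for comparing arms. No such record is mentioned for GCS or MSQ.

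**Step 2. There is no planned figure to reproduce.** The total of 30 (1:1, so 15 per arm) comes from a recommendation for pilot trials. The article gives no mean, SD or effect size for the daily scores, so everything below is illustration under stated assumptions.

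**Step 3. Effect of the RASS range alone, with no treatment effect.** Assume the same underlying RASS distribution in both arms, normal with mean m and SD s. Controls are read without restriction. Intervention readings are kept only at RASS −2 to +2, which is −2.5 to +2.5 on the continuous scale. The shift in the mean is

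shift = s × [φ(a) − φ(b)] / [Φ(b) − Φ(a)], with a = (−2.5 − m)/s and b = (2.5 − m)/s.

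- m = 0, s = 1.5: a = −1.667, b = 1.667. By symmetry φ(a) = φ(b), so the shift is 0.
- m = −1.5, s = 1.5: a = −0.667, b = 2.667. Shift = 1.5 × (0.3194 − 0.0114)/(0.9962 − 0.2525) = 1.5 × 0.3080/0.7437 = +0.62. About 74% of readings are in range.
- m = −2, s = 1.5: a = −0.333, b = 3.0. Shift = 1.5 × (0.3774 − 0.0044)/(0.9987 − 0.3694) = 1.5 × 0.3730/0.6293 = +0.89. About 63% are in range.

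**Step 4. What a t test would do with this.** This is a simulation with integer RASS from −5 to +4, 15 patients per arm, one reading each, a two-sided 5% t test, 20,000 runs and no treatment effect. The article does not state sidedness; two-sided is assumed.

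| Underlying mean (SD 1.5 to 2.0) | Shift in mean RASS | False-positive rate | Same rule in both arms |
|---|---|---|---|
| 0 | 0.0 to +0.05 | 5% | 5% |
| −1 | +0.4 to +0.55 | 12 to 15% | 5% |
| −2 | +0.9 to +1.1 | 45 to 46% | 5% |

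A mean of −3 gives more still (+1.4 to +1.5), but then only 39 to 45% of readings would permit a session.

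Stated without a RASS model, an assumed pure timing shift of 0.25, 0.5 or 0.75 SD gives a false-positive rate of 10%, 26% or 51% with 15 per arm.

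**The case against.** The strongest reply is that the trial does not rest on these scores. That is right. The progression criteria in Table 1 are recruitment, retention, completion of the intervention, administration of the measures and adverse events. The phase III sample size is to come from the primary outcome, FIM, which is assessed blind at the same points in both arms. MBI, MoCA, grip strength, HADS and SF-36 also share their post-ICU time points across arms. The article says the trial is not powered for clinically significant change. This lowers the priority of the point but does not remove it.

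A second reply is that no between-arm test of the daily scores is clearly planned. Group comparisons are described at each follow-up, the abstract treats GCS, RASS and CAM-ICU as daily measures apart from the secondary ones, and Table 3 uses all four scores to choose tasks. The secondary list even contains IQCODE, which is only a screening tool. This has some force. However, the scores stand under the secondary outcome heading, controls have their own collection time, and the intervention effect is to be analysed through the listed measures without exception.

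A third reply is that session RASS and CAM-ICU are for additional analysis, on top of the nursing record. That may be the intention, but it covers two of the four scores. How daily scores are summarised could be left to an analysis plan, but when they are collected could not: a 9 am MSQ never given in the intervention arm cannot be recovered later.

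The illustration has its own limits. RASS is measured to decide suitability, so out-of-range values may be recorded; the article does not say whether they are kept. It also does not say whether controls have sedation breaks, or whether any coincide with 9 am.

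A reader might infer from all this that the arms will certainly differ, or that delirium detection is grossly inflated. The documents support neither. With an assumed 30% positive per reading, six readings would give 1 − 0.7⁶ = 88% with any positive, but that needs six independent readings, although each pair brackets one short session. It also needs an any-positive-that-day endpoint, which the protocol does not name.

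**Conclusion.** The point holds as a should-fix. The article fixes reading rules by arm for four listed secondary outcomes, so timing, sedation state, days and number of readings are confounded with allocation in any between-arm comparison of them. Bias can be expected even with no treatment effect.

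Its size and direction cannot be derived from the documents. For RASS the shift runs from about 0 if patients centre on 0 to about +1 if they centre on −2. This assumes SDs of 1.5 to 2.0 and that out-of-range readings in the intervention arm are not kept. For CAM-ICU the net direction is open: selecting more alert states and taking more readings may pull opposite ways. The conclusions on FIM, the discharge and 90-day measures and progression do not depend on this point.

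**What to change.** State that any between-arm comparison of RASS, CAM-ICU, GCS and MSQ uses one reading rule: the 9 am score on every ICU day in both arms, including weekends and days without therapy.

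- Take RASS and CAM-ICU from the routine nursing scores, and define how close to 9 am an entry must be.
- Record GCS and give the MSQ at 9 am in the intervention arm as well.
- Keep the pre- and post-session scores for tailoring sessions and for within-arm description, and state that they are not compared with controls.

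The cost is case report form and analysis wording, plus a few minutes a day for the added GCS and MSQ in about 15 patients. The Control group section puts the whole daily set at no more than 10 min. A protocol change also needs ethics approval and notice to the registry, as the Ethics/governance section provides. Recruitment is described as paused, so the change could be in place before further patients enter; MSQ readings not taken at 9 am in intervention patients already treated are lost for this comparison.
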